#### Interim analyses {21b}

Not applicable.

#### Methods for additional analyses (e.g. subgroup analyses) {20b}

Not applicable.

#### Methods in analysis to handle protocol non-adherence and any statistical methods to handle missing data {20c}

Due to the anticipated small number of missing data, we will dispose missing data by transfer the last data to the final data. The data of this participant will be entered into the Full Analysis Set (FAS) in an invalid way, and this case will not be entered into the Per Protocol Set (PPS). Finally, the statistical significance of FAS and PPS will be analyzed. If the statistical significance was consistent, there was statistical difference.

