#### Criteria for discontinuing or modifying allocated interventions {11b}

Participants will be free to withdraw from the clinical study and choose other treatments (e.g. citicoline sodium tablets) if they feel their disease will not improve. Reasons for discontinuation of treatment may include but are not limited to, the following reasons: (1) participant becomes pregnant; (2) participant experiences serious side effects or complications; (3) participant takes other medicine during the study; (4) participant does not comply with the study protocol; and (5) participant requests withdrawal for other reasons.

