### Participant timeline {13}

#### Sample size {14}

The calculation of the sample size is based on previous studies. The effective rate of mecobalamin tablets for GPCI was approximately 85% [17, 18], We hypothesized a 90% effective rate of BJYSP for GPCI in a larger sample size. According to the sample size of the estimation formula [19], α = 0.05, β = 0.10, in a two-sided test, P1 = 0.67, P2 = 0.871, two-sided u_α/2_ = u_0.05/2_ = 1.96, one-tailed u_β_ = u_0.1_ = 1.282. We put these values into the formula n^1^ = n^2^= $$ \frac{1}{2}{\left[\frac{{\mathrm{u}}_{\upalpha /2}+{\mathrm{u}}_{\upbeta}\ }{\sin^{-1}\sqrt{p_1}-{\sin}^{-1}\sqrt{p_2}}\right]}^2 $$, resulting in n^1^ = n^2^= $$ \frac{1}{2}{\left[\frac{1.96+1.282\ }{\sin^{-1}\sqrt{0.67}-{\sin}^{-1}\sqrt{0.871}}\right]}^2=87.86. $$ That is, approximately 88 cases in the BJYSP group and in the control group or 176 cases in both groups. To account for a 20% dropout rate, the calculation 176 + (176 × 20%) = 211.2 suggests that 212 patients should be recruited. We rounded this value to 216 patients in total.

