### Statistical methods

#### Statistical methods for primary and secondary outcomes {20a}

Statisticians will independently undertake statistical analysis. All data will be presented as the means ± standard deviation (SD). Statistical analysis will be performed by SPSS 21.0 software (SPSS Inc., Chicago, IL, USA). All statistical tests will be two-sided tests, and the statistical significance threshold will be set at *P* < 0.05. The chi-square test will be used for categorical variables, an independent Student’s t-test will be used on measurement data, and rank-sum test will be used for grade data. To assess covariate balance, baseline characteristics will be summarized and compared between the BJYSP group and the control group by means of simple descriptive statistics.

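### The FAS/PPS rule in {20c}, as written, calls two non-significant results a difference and gives no verdict when the two sets disagree

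*Protocol article*

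**What the plan says.** The section on non-adherence and missing data, {20c}, carries the last value forward for missing data. Of a participant with missing data it says: "The data of this participant will be entered into the Full Analysis Set (FAS) in an invalid way, and this case will not be entered"; the set meant by the last words is the PPS. It continues: "Finally, the statistical significance of FAS and PPS will be analyzed". The decision rule follows directly: "If the statistical significance was consistent, there was statistical difference".

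The statistical methods section, {20a}, sets the threshold for each single test: "All statistical tests will be two-sided tests, and the statistical significance threshold will be set at" P < 0.05. It does not say which analysis set decides, or how two results are combined. No other section of the article completes the rule in {20c}.

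Two statements bear on how far the sets may differ. {20c} opens with "Due to the anticipated small number of missing data", while the sample size section, {14}, adds patients "To account for a 20% dropout rate". Under the blinding section, {17a}, participants and treating clinicians know the assignment.

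**The concern.** The rule turns on whether the two results agree, not on whether they are significant. Agreement covers two situations, both significant and both non-significant, and the sentence attaches the same conclusion to each. For disagreement it attaches none, so that conclusion would be chosen after the results are known.

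If the intended meaning is that both sets must be significant, a different problem remains. The PPS leaves out participants according to something that happens after randomisation, namely missing data. In an open-label comparison, who stays and who leaves can differ by arm. A conclusion that needs the PPS therefore rests partly on a comparison that randomisation no longer protects, and power is lost. At stake is how the trial's result is declared.

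**Working it through.** **Step 1. The written rule, case by case.**

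| FAS | PPS | Consistent? | Conclusion as written |
|---|---|---|---|
| significant | significant | yes | difference |
| not significant | not significant | yes | difference (wrong) |
| significant | not significant | no | none stated |
| not significant | significant | no | none stated |

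One case in four is handled properly.

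**Step 2. The plan's own figure.** {14} uses "α = 0.05, β = 0.10, in a two-sided test, P1 = 0.67, P2 = 0.871". With the arcsine formula given there, asin√0.67 = 0.9589 and asin√0.871 = 1.2034, a difference of 0.2446. Then n = ½ × (3.242 / 0.2446)² = 87.86, or 88 per group, as stated. The 1.96 + 1.282 = 3.242 is the mean of the test statistic at 90% power and is used in step 4.

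**Step 3. No true effect.** Treat the FAS and PPS statistics as bivariate normal with unit variances and correlation ρ, each tested two-sided at 0.05 (critical value 1.96). The documents give no ρ. If the PPS were a random 80% of the FAS (the 20% dropout in {14}), ρ would be √0.8 = 0.894. I use 0.9, with a range of 0.70 to 0.95.

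| ρ | both significant | both non-significant | discordant |
|---|---|---|---|
| 0.70 | 0.017 | 0.917 | 0.067 |
| 0.90 | 0.030 | 0.930 | 0.041 |
| 0.95 | 0.035 | 0.935 | 0.029 |

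Literal rule: a difference is declared in 1 − 0.041 = 0.959 of null trials (0.933 to 0.971 over the range). Rule read as significance in both sets: 0.030 (0.017 to 0.035), below 0.05.

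**Step 4. A true effect, FAS power 90% (mean 3.242).**

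(a) Equal power in both sets.

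(b) PPS 20% smaller with the same effect: mean 3.242 × √0.8 = 2.900, so power in the PPS alone is Φ(2.900 − 1.96) = 0.826.

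| | ρ | both significant | both non-significant | discordant |
|---|---|---|---|---|
| (a) | 0.70 | 0.847 | 0.047 | 0.106 |
| (a) | 0.90 | 0.869 | 0.069 | 0.062 |
| (a) | 0.95 | 0.878 | 0.078 | 0.044 |
| (b) | 0.70 | 0.791 | 0.064 | 0.145 |
| (b) | 0.90 | 0.814 | 0.088 | 0.098 |
| (b) | 0.95 | 0.822 | 0.095 | 0.083 |

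At ρ = 0.9, requiring both costs 90% − 87% = 3 points in (a) and 90% − 81% = 9 points in (b). No conclusion is stated in about 6% or 10% of these trials.

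**Step 5. Does the 20% allowance remove the loss?** If all 216 are in the FAS, its mean is 3.242 × √(216/176) = 3.592, with power Φ(1.632) = 0.949. A PPS of 0.8 × 216 = 172.8 has mean 3.242 × √(172.8/176) = 3.212, with power Φ(1.252) = 0.895. Power for both together cannot exceed 0.895, so the loss against the FAS alone is at least 0.949 − 0.895 = 0.054. The starting point is higher, but a loss of several points remains.

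**The case against.** The strongest reply is that nobody would apply the literal rule. {20a} ties significance to P < 0.05, the English of {20c} is uneven, and the natural sense is that significance appears in both sets. On that reading FAS significance is still required, so a distorted PPS cannot create a positive claim that the FAS does not support; it can only block one. This stands. The 96% figure describes the sentence, not how the trial is likely to behave.

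Three stronger inferences should also be resisted.

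- A reader might take the discontinuation reasons in {11b}, such as "participant does not comply with the study protocol", as PPS exclusions. That section concerns stopping treatment and does not mention the PPS; {20c} names only the participant with missing data. The full PPS definition may stand elsewhere.
- A reader might infer an inflated false-positive rate. Under the probable reading the rate falls below 0.05.
- A reader might describe this as a superiority rule. The article does not use that word; it can only be inferred from two-sided difference tests against an active control with no margin stated.

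It could also be said that the analysis plan will settle the matter. That would answer silence, but here the protocol states a rule. An analysis plan that copied it would carry the fault over, and one that departed from it would contradict the protocol.

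**Conclusion.** The rule is wrong as written and should be replaced. Two faults follow from the wording alone and need no assumption: a difference is declared from two null results, and no conclusion is given for discordant ones.

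Under the probable intent, type I error is controlled (about 3% at ρ = 0.9). The harm is then a conclusion that depends on a post-randomisation subset in an open-label trial, a fall in power from 90% to about 87% or 81%, and about 6% to 10% of such trials without a stated outcome.

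These sizes rest on an assumed ρ, the same true effect in both sets, and 90% power in the FAS. They are illustrative, because {14} sizes the trial on an effective rate while the primary variables in {12} are mean changes. Discordance is a realistic prospect, since {14} allows for 20% dropout even though {20c} expects little missing data.

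**What to change.** Replace the sentence in {20c} with:

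> For each primary outcome variable, a difference between groups is concluded only if the FAS comparison (all randomised participants, as randomised) is significant at two-sided 0.05; the PPS analysis is supportive, is reported alongside, and neither establishes nor overturns the FAS conclusion.

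The change is one sentence, made before database lock, with no new data, visits or patients. What is given up is the stricter requirement that the PPS agree; a reader can still see any disagreement because both results are reported.

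Two matters are not settled by this sentence. {12} lists 1 + 3 + 4 + 13 = 21 primary variables, so the wording is per variable and multiplicity needs its own treatment. And {20c} should say how a carried-forward value fits with entering the participant in the FAS as invalid, so that the deciding FAS comparison is fully defined.

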#### Plans to give access to the full protocol, participant-level data, and statistical code {31c}

No plans.

### Oversight and monitoring

#### Composition of the coordinating center and trial Steering Committee {5d}

The Steering Committee (SC) will be composed of the subject leader and the project manager. The SC responsible for the management of the whole project.

The inspectors of the Monitor Group (MG) are appointed by the SC. The MG monitored the whole process of the study in accordance with the GCP specification. The inspector monitors the investigator’s compliance with the protocol, protection of participants’ rights and interests, the quality of the CRF form, and the investigators’ knowledge of various standards and then writes the inspection reports to the SC.

#### Composition of the data monitoring committee, its role, and reporting structure {21a}

No data monitoring committee has been invited for this study because of the expected low incidence of adverse events and the low numbers in each center. Statistical package Epidata 3.1 will be used to build the database, routine data monitoring will be performed according to the standard operating procedures of sponsor. The trial is managed by the SC and with oversight from the MG.

#### Adverse event reporting and harms {22}

Adverse events, such as signs and symptoms and other discomforts, will be observed and recorded in detail during the study and follow-up phases. All adverse events will be strictly recorded, monitored, and treated until resolved.

#### Frequency and plans for auditing trial conduct {23}

Our trials will be audited every 6 months by the supervisor who has successfully completed pharmaceutical clinical trial and the review process will be independent of investigators and sponsors.

#### Plans for communicating important protocol amendments to relevant parties (e.g. trial participants, ethical committees) {25}

If there are changes to eligibility criteria, outcomes, and analyses, a new version of protocol will be submitted to the Medical Ethics Committee of the Affiliated Hospital of Chengdu University of Traditional Chinese Medicine for approval.

#### Dissemination plans {31a}

The results of the research will be presented in the form of publication or conference reports.

## Discussion

As the leading cause of irreversible blindness, glaucoma brings a huge burden to patients, families, and society. Therefore, developing medicines that protect visual function in patients with glaucoma has become a hotspot for public health [21]. Reducing IOP and neuroprotective treatments are presently the most practiced visual function protective therapeutic approach for glaucoma. However, progressive loss of vision or blindness can still occur in some patients with GPCI, and the neuroprotection for glaucoma remains unsatisfactory at present [22]. Therefore, exploring an effective neuroprotective agent for patients with glaucoma is important and urgent.

TCM harbors a long history and a unique advantage in treating neurodegenerative diseases, such as glaucoma [23]. BJYSP has been widely used in the treatment of GPCI, but useful empirical research is insufficient for its popularization and application. The disadvantages of less rigorous designs, small sample sizes, and low quality have led to many TCM studies being insufficient to convince people of its value.

In this trial, we will investigate whether BJYSP can effectively protect the optic nerve and improve visual function for GPCI. The mecobalamin tablets are currently being used as a routine treatment for treating visual function impairment of GPCI [15, 16]. Therefore, mecobalamin was chosen as a positive-control medicine in our trial. In addition, to observe the effect of BJYSP on GPCI with different disease severity, GPCI will be classified as early, moderate, and advanced based on the visual field defects of patients.

The PROBE design is not a double-blind, placebo-controlled trial, but the assessors, statisticians, and investigators who perform each examination on patients will be completely blinded to group allocation. In addition, a double-blind, placebo-controlled design would cause considerably higher costs compared with the PROBE design. Furthermore, the potential advantage of the PROBE design is that the effect of BJYSP will resemble the effect in clinical practice, and the PROBE design has been extensively proven to yield the same results as placebo-controlled designs [24, 25]. Nevertheless, to guarantee the quality of this study, the design and execution of the study will be strictly performed with proper quality control. A training session for each center will be held to explain the detailed study protocol, the diagnosis of the TCM syndrome pattern, and the SOPs. The same investigator will be responsible for the examination of each patient at different time periods. All indicators will be assessed by independent assessors. The principal investigators, statistician, and outcomes assessors will be blind to the treatment assignments until the database was locked.

In conclusion, the purpose of this research is to verify the therapeutic efficacy and safety of BJYSP. The outcome of the study will provide evidence-based data for the use of BJYSP to treat GPCI with liver-kidney deficiency, blood stasis, and fluid retention syndrome, thereby providing a new avenue in the treatment of GPCI.

### Trial status

Recruitment began in June 2018 and the approximate date when recruitment will be completed is April 2020. Protocol version 2.0 was approved on 6 April 2018.

## Data Availability

Not applicable.

## Abbreviations

GPCI: Glaucoma with controlled IOP
BJYSP: Bujing Yishi tablet
PROBE: Prospective, randomized, open-label, blinded endpoint
BCVA: Best-corrected visual acuity
VEP: Visual evoked potential
HRT II: Heidelberg Retina Tomography II
IOP: Intraocular pressure
TCM: Traditional Chinese medicine
RGCs: Retinal ganglion cells
RNFL: Retina nerve fiber layer
RGCL: Retinal ganglion cells layer;
GCP: Good Clinical Practice
SOPs: Standard operating procedures
AEs: Adverse events
CRF: Case report form
